CLINICAL STUDY PROTOCOL

EFFIPEC – Efficacy of Hyperthermic Intraperitoneal Chemotherapy
Single-arm Phase I study, followed by an open-label, randomized, controlled
registry-based phase III trial

| **Sponsor Project No:** | EFFIPEC |  |
| --- | --- | --- |
| **EudraCT number:** | 2020-005210-18 |  |
| **Investigational Product:** | 5-Fluorouracil and Irinotecan |  |
|  |  |  |
| **Sponsor:** | Uppsala University |  |
| **Sponsor Representative:** | [name], PhD  [contact]  E-mail: [contact] |  |
| **Coordinating Investigator:** | [name], PhD |  |
| **Investigators:** | [name], PhD (PI)  [name], PhD (PI)  [name], PhD (PI)  [name], PhD (PI) |  |
|  |  |  |
| **The clinical study will be conducted, and essential documentation archived, in compliance with relevant UCR SOPs and standards, which incorporate the requirements of the ICH Guideline for Good Clinical Practice.** | | |

| **SYNOPSIS** | | |
| --- | --- | --- |
| Title of study:   EFFIPEC – Efficacy of Hyperthermic Intraperitoneal Chemotherapy (HIPEC) | | |
| Name of Sponsor/Company: Uppsala University/[name] | | |
| Name of investigational product: 5-Fluorouracil and Irinotecan | | |
| Investigator(s) and study center(s): |  | |
| [name] & [name], PhD | Uppsala University Hospital | |
| [name], PhD | Skåne University Hospital | |
| [name], PhD | Sahlgrenska University Hospital | |
| [name], PhD  Pending approval  Pending approval | Karolinska University Hospital  Aarhus University Hospital, Denmark  Oslo University Hospital, Norway | |
| Planned study period:  2021-01-01 to 2029-12-31 | | Phase of development:  Phase I/III |
| Objectives:  Primary objectives:  Phase I: To determine the maximum tolerated dose of 5-Fluorouracil 24-hour EPIC, in combination with intensified oxaliplatin/irinotecan HIPEC, for treatment of colorectal cancer.  Phase III: To study the recurrence-free survival (RFS) of patients 12 months after treatment  Secondary objectives:  Overall and recurrence-free survival up to 5 years  Postoperative complication rates within 30 days  Quality of life of patients up to 3 years after study treatment | | |
| Methodology:  A combined phase I/III trial, consisting of an initial dose titration study followed by an open-label, randomized controlled study. | | |
| Number of subjects (planned):  Dose escalation study: min 15 and max 30 patients - Number of patients is based on toxicity observed.  Efficacy study: 326 patients. Interim analysis is done after 140 patients are included | | |
| Diagnosis:  Colorectal cancer | | |
| Inclusion criteria:   1. Provision of written informed consent prior to any study specific procedures. 2. ECOG Performance Status Score 0,1 or 2 alternatively Karnofsky 60-100 3. Adequate kidney, liver, bone marrow function according to laboratory tests 4. For females of childbearing potential, a negative pregnancy test must be documented 5. ≥ 18 years old and <75 years old 6. Colorectal cancer with peritoneal metastases +/- liver metastases (maximum 3) 7. All patients deemed eligible for CRS and HIPEC according to clinical routine management during a HIPEC multidisciplinary board at each respective hospital can be included. | | |
| Exclusion criteria:   1. Previous severe toxicity/allergic reactions to systemic chemotherapy agents oxaliplatin or irinotecan or 5-fluorouracil 2. Unable to tolerate intensified HIPEC treatment due to comorbidity 3. Metastasis other than peritoneum or liver 4. Complex liver-perenchymal sparing surgery or hemihepatectomy procedures are to be excluded. 5. Previous CRS or HIPEC 6. Pregnant or lactating (nursing) women 7. Active infections requiring antibiotics 8. Active liver disease with positive serology for active hepatitis B, C, or known HIV 9. Concurrent administration of any cancer therapy other than planned study treatment within 4 weeks prior to and up to 4 weeks after study treatment 10. Incomplete cytoreduction defined as completeness of cytoreduction score 1-3 11. Histopathology of other origin than colorectal cancer | | |
| Investigational product, dosage and mode of administration:  Injection of irinotecan 360 mg/m^2^ and 5-fluorouracil 24-hr EPIC 250-850 mg/m^2^ in combination with Oxaliplatin 360 mg/m^2^ and an intraoperational IV of 5-fluorouracil bolus 400 mg/m^2^ with calcium folinate 60mg/m^2^.  The EPIC treatment is given after the abdomen is completely sutured in the operating theatre. The dose will be divided equally into 2 injections á 200ml each through two abdominal drains. | | |
| Duration of treatment:  24 hours | | |
| Active control, dosage and mode of administration:  Injection of oxaliplatin 460 mg/m^2^ and an intraoperational IV of 5-fluorouracil 400 mg/m^2^, and calcium folinate 60 mg/m^2^ | | |
| Criteria for evaluation:  Safety: Safety will be assessed by the Clavien-Dindo classification and reporting of Adverse Events.  The maximum tolerated dose of 5-FU will be determined by giving the first 15-30 patients escalating doses of 5-FU. The morbidity of each dose level of 5-FU 24-hour EPIC will be evaluated by the Data Monitoring Committee 30 days post-treatment. A dose level with ≤1/3 or ≤2/6 with 3b-4 Clavien-Dindo morbidity may proceed to the next dose level. Following the dose titration study, all patients will receive the maximum dose of 5-FU. An interim safety evaluation will be performed after the first 140 patients have been randomized and treated with HIPEC or HIPEC in combination with EPIC. The Clavien-Dindo grade 3-5 morbidity is expected to be approximately 0.35 (35%). If the experimental arm’s 95% CI falls within 0.4 or below, the study will be allowed to continue.  Efficacy: Recurrence free survival (RFS) is determined at 12-months post treatment through the HIPEC registry. Postoperative complications rates with-in 30 days, 5-year overall survival and RFS are further determined through the HIPEC registry and quality of life is assessed by questionnaires through the QoL registry. | | |
| **Dosage of Investigational Products:**  The maximum tolerated dose (MTD) of 5-FU will be determined by giving the first 15-30 patients escalating doses of 5-FU. The morbidity of each dose level of 5-FU 24-hour EPIC will be evaluated by the Data Monitoring Committee within 30 days post-treatment. A dose level with ≤1 of 3 patients or ≤2of 6 patients (extended group size) with 3b-5 morbidity may proceed to the next dose level. If the frequency of 3b-5 morbidity is higher, MTD has been passed and the dose of 5-FU in the efficacy study will be the next lower dose level. If MTD is not reached the highest dose level of 5-FU (850 mg/m^2^) will be used. | | |
| Statistical methods:  Recurrence free and overall survival of the two arms will be compared using the parameters: treatment arm, age, PCI, CC score, use of systemic perioperative chemotherapy (neoadjuvant and/or adjuvant), concomitant liver metastases resection, colon or rectal primary tumor, and lymph-node metastasized primary tumor.  QoL will be analyzed by comparing the answers to questions 29 and 30 in QLQ-C30 by Mann-Whitney U test and Freidman’s repeated measures ANOVA test. Specifically, differences between the sexes will be investigated.  Statistical significance will be set at p=0.05. | | |

# List of abbreviations AND DEFINITIONS OF TERMS

5-FU 5-fluorouracil

AE Adverse Event

CIOMS Council for International Organizations of Medical Sciences

CRCPM ColoRectal Cancer with Peritoneal Metastases

CRF Case Report Form

CRS Cytoreductive surgery

CC score Completeness of cytoreduction score

DCF Data Clarification Form

DMC Data Monitoring Committee

EPIC Early Postoperative Intraperitoneal Chemotherapy

EOS End of study

ERA Ethical Review Authority

G-CFS Granulocyte Colony Stimulating Factor

GCP Good Clinical Practice

HIPEC Hyperthermic IntraPEritoneal Chemotherapy

IEC Independent Ethics Committee

IMP Investigational Medicinal Product

MPA Medical Products Agency

PI Principal Investigator

QoL Quality of Life

RFS Recurrence-Free Survival

SAE Serious Adverse Event

SUSAR Unexpected Serious Adverse Reaction

UCR Uppsala Clinical Research Center

# BACKGROUND INFORMATION

## Investigational drugs

Irinotecan is an antineoplastic enzyme inhibitor primarily used in the treatment of colorectal cancer. It is a derivative of camptothecin that inhibits the action of topoisomerase I. 5-fluorouracil (5-FU) is a nucleobase analogue that is uracil in which the hydrogen at position 5 is replaced by fluorine. It is an antineoplastic agent which acts as an antimetabolite - following conversion to the active deoxynucleotide, it inhibits DNA synthesis (by blocking the conversion of deoxyuridylic acid to thymidylic acid by the cellular enzyme thymidylate synthetase) and thereby slows tumour growth. Both drugs are well known as systemic chemotherapy treatments of colorectal cancer. The side-effects are also well known and well-studied for many years. This trial is investigating a new combination treatment for colorectal cancer with peritoneal metastases. It is a treatment administered at the time of surgery.

## Disease background and preliminary efficacy

Colorectal cancer with peritoneal metastases (CRCPM) is now routinely treated with cytoreductive surgery (CRS) and hyperthermic intraperitoneal chemotherapy (HIPEC). A recent study, PRODIGE 7, has cast some doubt on the efficacy of oxaliplatin-based HIPEC for CRCPM [1, 2]. Due to some limitations in the PRODIGE 7 study, follow-up trial discussions have been difficult. However, there is a proof of concept from both gastric cancer and ovarian cancer (relatively chemoresistant [gastric] and chemosensitive solid tumors [ovarian]) that CRS +/- HIPEC has shown a benefit for patients treated with HIPEC [3, 4]. Thus, it seems clinically relevant and meaningful to continue the search for a HIPEC treatment that is effective in colorectal cancer. In two recent studies, there is a disease-free survival benefit in favor of oxaliplatin/irinotecan HIPEC vs single drug oxaliplatin HIPEC [5, 6]. Combination or intensified HIPEC treatment leads to increased recurrence-free survival (RFS), particularly peritoneal recurrence-free survival. Figure 1 demonstrates a significant benefit with each step of HIPEC intensification [5].

**Figure 1 [6]** – Colorectal cancer with peritoneal metastases treated with HIPEC +/-EPIC. The blue line represents the least intense perioperative intraperitoneal chemotherapy treatment, while the green and red lines represent stepwise intensified perioperative intraperitoneal chemotherapy treatment.

## Justification of administration route

The concept of both HIPEC and early postoperative intraperitoneal chemotherapy (EPIC) is to maximize the effect of chemotherapy on the peritoneum in order to prevent locoregional recurrence. The surgical treatment (cytoreductive surgery) is aimed at removing all visible tumor tissue from the peritoneum. The aim of the perioperative chemotherapy treatments of HIPEC and EPIC is then to eradicate potentially remaining microscopic peritoneal disease. It is well-known that the chemotherapy distribution from the bloodstream to the peritoneal cavity is limited due to the blood-peritoneal barrier. Therefore, this trial is using two intraperitoneal chemotherapy treatment options instead of systemic chemotherapy.

## Justification of Study design

The reason for going from a phase I to III combined approach is that the triple drug treatment (oxaliplatin, irinotecan, and 5-FU) has already been used in the medical oncology clinic as a routine clinical treatment for many years with a well-known and reported toxicity profile; and it has also, in some countries, been used in the HIPEC setting with 5-days of 5-FU EPIC. The initial plan was to do a direct phase III study. However, since it is planned to give a single dose of 5-FU instead of 5 daily treatments, it will probably be possible to increase the concentration of 5-FU EPIC. As such, the study committee opted to do a dose-titration study (phase I) including 15-30 patients to evaluate the possibility of using a slightly higher single dose 24-hour 5-FU. Instead of a phase II trial, an interim analysis after treatment of the first 140 patients in phase III was added to evaluate safety and aim for a phase III final comparison including 326 patients.

The rationale behind two investigational drugs (irinotecan and 5-FU) is that adding only one drug is not enough to provide a synergy that can produce a reasonable investigational clinical effect (see figure 1). The dose-titration of irinotecan to oxaliplatin HIPEC has already been performed [14]. Thus, the phase I part of the trial is investigating the addition of 5-FU EPIC in a dose-titration manner to oxaliplatin + irinotecan HIPEC. The phase III part of the trial requires both drugs to be added for efficacy reasons and it is not feasible clinically to have several trial arms. Since the triple drug combination has already been in use in France with cytoreductive surgery and the combination is well studied and in use in clinical routine medical oncology treatment for metastasized colorectal cancer, it is the synergy of all three drugs combined with cytoreductive surgery that is being studied in phase III. Hence, all conclusions will be related to the combination treatment as such.

The risks of adding 5-FU EPIC to HIPEC has been reviewed already in several trials [7]. The risk of morbidity, reoperation, or postop mortality is not increased [6]. Although, one particular side-effect of neutropenia is expected to increase, it does not increase the risk of other morbidity [8]. In order to offset this side-effect, a planned bone marrow stimulation treatment will be administered.

## Study population

The trial concerns patients with colorectal cancer and peritoneal metastases. The total number of patients possibly eligible for the study will be about 120 patients per year in Sweden.

## Compliance with GCP and regulatory requirements

This study will be conducted in compliance with this protocol and in accordance with the Good Clinical Practice guidelines (ICH-GCP), the principles of the Declaration of Helsinki and according to applicable regulatory regulations and directives.

The study will not start until the protocol has been approved by the Ethical Review Authority (Etikprövningsmyndigheten) and the Medical Products Agency (Läkemedelsverket).

# STUDY OBJECTIVES

## Primary objectives

### Phase I

Phase I: To determine the maximum tolerated dose of 5-Fluorouracil 24-hour EPIC, in combination with intensified oxaliplatin/irinotecan HIPEC, for treatment of colorectal cancer.

### Phase III

## Phase III: To study the recurrence-free survival (RFS) of patients 12 months after treatment. secondary objectives

1: Overall and recurrence-free survival up to 5 years,

2: Postoperative complication rates within 30 days

3: Quality of life of patients up to 3 years after study treatment

# ENDPOINTS

## Primary Endpoint

### Phase I

- Maximum tolerated dose of 5-FU 24-hour EPIC. Possible toxicity will be reported as Adverse Events.

### Phase III

- Recurrence-free survival at 12 months.

## Secondary Endpoints

The secondary endpoints are to evaluate the:

- Overall survival and RFS up to 5 years through the HIPEC registry
- Postoperative complication rates within 30 days
- Quality of life of patients up to 3 years after treatment

# STUDY DESIGN

## Study outline

A dose titration study and a combined superiority registry-based open-label randomized control trial is planned to answer the trial objectives. The study will be registry-based to allow simpler and more comprehensive follow-up. Patients with colorectal cancer will be treated with cytoreductive surgery (CRS) together with either standard oxaliplatin HIPEC (the control for the efficacy study) or oxaliplatin/irinotecan HIPEC in combination with 5-FU 24-hour EPIC. The 5-FU will be administered postoperatively when the abdomen is completely sutured. The drug is divided equally into 2 injections of 200 ml each and injected through two abdominal drains that are clamped for 16hours.

For dose escalation, the titration groups (á 3 or 6 patients) are followed for 30 days postoperatively after which the Data Monitoring Committee (DMC) will determine whether or not to increase the 5-FU dose for the following group of patients.

To study efficacy, randomization is performed intraoperatively. The patient is followed up postoperatively for a total of 3 years for the secondary endpoints which may be extended by the study committee to 5 years. Since the trial is registry based, the long-term follow-up does not require separate eCRF evaluations. These evaluations can be automatically retrieved from the registry – both recurrence data, quality of life, and morbidity data. Some specific eCRF evaluations will be integrated as a separate study part of the HIPEC registry, such as inclusion/exclusion criteria and adverse event reporting (including SUSAR reporting).

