## END OF STUDY

The end of study (EOS) is defined as 5 years after the last patient was included in the study, when long-secondary outcomes can be evaluated.

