## Clinical and laboratory assessments

### Timing and method of the assessment

The dose titration is assessed continuously as each dose level is completed. All morbidity data is retrieved from the HIPEC registry.

Patient follow-up:

Mandatory

- Abdominal and thoracic CT scan at baseline before surgery and 12 months postoperatively.
- Treatment administered (CRS+HIPEC+EPIC variables)
- Morbidity to be submitted within 30 days from treatment administration. SAE and SUSAR are to be reported immediately (a separate section will make this possible in the HIPEC registry)
- Overall survival follow-up at
- 5 years from the HIPEC registry

Clinical routine

- The following follow-up is standard in Sweden after CRS+HIPEC: CT scan and tumor markers every 6 months for 2 years and then annually for another 3 years. Since all these follow-ups are not included in the HIPEC registry, we will not include them in the schedule of investigational events.
- EORTC QLQ-C30, CR29, and STO22 questionnaires filled out at baseline, 3, 12 and 36 months after surgery using the established QoL database. All patients are included in the quality-of-life registry as part of the clinical quality assurance follow-up, unless they specifically have requested not to be included.

Optional: Sending intraoperative tumor tissue to Uppsala for chemoresistance testing within 48 hours. Tissue is discarded right after testing. No biobanking will occur.

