#### Interim analysis

The Clavien-Dindo grade 3-4 morbidity is expected to be approximately 0.35 (35%) for patients receiving the maximum dose of 5-FU. Allowing for a small increase in morbidity to 0.40 and an accepted 95% confidence interval width of 0.15, at least 66 patients are needed in the experimental arm to determine whether the arm deviates from the expected morbidity rate. The total sample size will be 140 (70 per arm) for an interim trial safety evaluation (circa 50% of trial included). If the Clavien-Dindo grade 3-4 morbidity falls outside of the 40% mark, then a Fisher’s exact test comparison between the standard and experimental arm will be performed together with a mortality comparison. Concerning in-hospital mortality, a maximum rate of 5% will be set. This planned interim safety evaluation will be unpublished. If the morbidity is increased beyond the set mortality limit or the increase is of a more serious nature, the trial will either be discontinued or alternatively, depending on the character of the complications, a lower dose level may be employed.

The overall survival and recurrence free survival will be reviewed during this interim safety evaluation to see if a primary endpoint of overall survival is attainable with increased cohort size instead of 12-month RFS. If attainable depending on inclusion rate, the endpoint will be changed, and a new sample size calculation will be performed. Likewise, a choice between 3 or 5 year follow-up will be made. Alternatively, trial futility will be determined if no differences at all are forthcoming even in the RFS setting. In this case, the trial will close prematurely. A decision to close the trial is made by the sponsor in conjunction with site investigators.

Possible changes of dose level, endpoint, sample size calculation or other substantial changes will be submitted to the MPA and ERA as an amendment to the protocol.

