##### Secondary outcome analyses of overall survival and QoL:

- Overall survival up to 5 years will be compared with Kaplan-Meier and log-rank test as well as multivariable Cox regression using the following same variables as RFS: Treatment arm, age, PCI, use of systemic perioperative chemotherapy (neoadjuvant and/or adjuvant), liver metastases resection, colon or rectal primary, and lymph-node metastasized primary tumor.
- Quality of life between the two arms will be compared. The primary outcome is the comparison of questions 29 and 30 from the QLQ-C30 at 12 months and 36 months. The primary statistic will be a Mann-Whitney U test of difference for both question 29 and 30 between the arms. The secondary statistic will be a comparison of mean differences for question 29 and 30 between baseline and 12-months using a Freidman’s repeated measures ANOVA test. Specifically, differences between the sexes will be investigated.
- Three specific subgroup multivariable analyses using RFS as endpoint will be performed using the same variables as above for correction: (1) PCI score – the score will be grouped 1-10, 11+, (2) Signet cell cancer, (3) previously given oxaliplatin-based therapy, (4) +/- livermetastases.
- Further exploratory and post hoc analysis of subgroups will be performed: multivariable analysis for overall survival and forest plots.

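### The follow-up horizon for secondary OS and RFS is 3 years (extendable) in the study outline, left open until the interim in the statistics section, and 5 years in the objectives, endpoints, schedule and OS analysis

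*Protocol*

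**What the plan says.** Two places in the protocol treat the horizon as open:

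- Section 8.1 (Study outline) wants participants "followed up postoperatively for a total of 3 years for the secondary endpoints which may be extended by the study committee to 5 years".
- Section 13.2.1 (Interim analysis), directly after saying that OS and RFS will be reviewed: "Likewise, a choice between 3 or 5 year follow-up will be made". No decision-maker and no criterion are given for this choice.

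The other places that state a horizon for OS or RFS give 5 years and attach no condition:

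- Section 6.2 and the synopsis: "Overall and recurrence-free survival up to 5 years".
- Section 7.2: "Overall survival and RFS up to 5 years through the HIPEC registry".
- Section 8.3, Table 3: OS is ticked at year 5, and RFS at years 1, 3 and 5.
- End of study, after Table 3: "The end of study (EOS) is defined as 5 years after the last patient was included in the study".
- Section 11.1.1, mandatory OS follow-up: "5 years from the HIPEC registry".
- Section 13.2.1, secondary analyses: "Overall survival up to 5 years will be compared with Kaplan-Meier and log-rank test as well as multivariable Cox regression".

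Quality of life is the one secondary endpoint fixed at 3 years (Sections 6.2 and 7.2).

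**The concern.** A time-to-event comparison is not fully specified until its horizon is. The horizon decides which deaths and recurrences enter the log-rank and Cox analyses. Here the protocol gives 3 years, 5 years, and a decision still to be made.

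The interim text is the more serious of the two outlying passages. It places the choice at the same evaluation at which OS and RFS are looked at. That look compares the arms, because the futility rule in the same paragraph turns on whether differences between them are emerging. The treatment is unblinded (Section 10.5). A horizon chosen after such a look is no longer pre-specified with respect to the data it governs.

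It is also unclear who holds the decision: 8.1 names the study committee, and the interim text names nobody. The same paragraph allows OS to replace 12-month RFS as the primary endpoint. If that happened, the open horizon would belong to the primary analysis.

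**Working it through.** **1. Which horizon fits the calendar.** Section 13.3 gives 6 months for dose titration and Section 20.5 gives 3.5 years of inclusion.

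- With 5 years of follow-up after the last inclusion: 0.5 + 3.5 + 5 = 9.0 years.
- With 3 years: 0.5 + 3.5 + 3 = 7.0 years.

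The synopsis plans 2021-01-01 to 2029-12-31, which is 9 years. The timetable was built for 5 years.

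**2. The plan's own figure.** Section 13.3 states 148 per arm for 12-month RFS of 50% against 66%, alpha 5% (taken as two-sided) and power 80%.

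- The pooled two-proportion formula without continuity correction gives 149. The arcsine formula gives 147.95, that is 148.
- 148 × 1.10 = 162.8, that is 163 per arm and 326 in total.

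The stated size reproduces. It depends only on 12-month RFS, so the 3-or-5-year question does not touch it. The protocol states no OS rate, OS event count or OS power, so there is no corresponding OS figure to reproduce.

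**3. Share of 5-year deaths that fall in years 3-5, horizon counted per patient.** With exponential survival, S5 = S3^(5/3), and share = (S3 − S5)/(1 − S5). The S3 values are assumptions. The nearest figures in the document are in Table 4: 3-year OS of 46% and 50% in a mixed colorectal and high-grade appendix cohort, and OS of 19 and 38 months in another cohort (read here as medians).

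- S3 = 0.46: S5 = 0.274, share = 0.186/0.726 = 25.6%.
- S3 = 0.50: S5 = 0.315, share = 0.185/0.685 = 27.0%.
- Median 19 months: S3 = 2^(−36/19) = 0.269, S5 = 0.112, share = 17.7%.
- Median 38 months: S3 = 2^(−36/38) = 0.519, S5 = 0.335, share = 27.6%.
- S3 = 0.70 (a high value, for the range only): S5 = 0.552, share = 33.1%.

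Replacing the exponential by a Weibull with shape 0.8 to 1.5, at S3 of 46-50%, gives 22-36%.

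**4. The same with one calendar cut-off, 3 or 5 years after the last inclusion.** Accrual is 100 per year (Section 20.5), so A = 326/100 = 3.26 years. With λ = −ln(S3)/3, and the same rate applied to both arms, deaths by a cut-off F years after last inclusion are 326 × [1 − e^(−λF)(1 − e^(−λA))/(λA)].

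- S3 = 0.46: 225 deaths at F = 3 and 266 at F = 5. The later cut-off contributes 15.4% of the total.
- S3 = 0.50: 211 and 254, or 16.7%.

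**5. How much is known when the choice is made.** The interim follows 140 patients. At 100 per year that is about 1.4 years after randomization begins. Table 3 notes that OS is taken from the registry before the interim. The data seen would be early but real.

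**The case against.** The best defence is that 3 years describes active follow-up only. In Table 3 the telephone contacts and questionnaires end at year 3, and the year-5 column holds only OS and RFS from the registry. Section 8.1 itself goes on to say that long-term follow-up needs no separate eCRF evaluations. On this view nothing conflicts. The reading fails on two counts. The sentence in 8.1 concerns the secondary endpoints, and Section 7.2 lists OS and RFS first among them. The interim text also presents the 3-or-5-year horizon as undecided. Reading 5 years as a mere ceiling does not help either, because the end-of-study definition and Table 3 are not worded as ceilings.

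Other parts of the defence stand:

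- The OS analysis text names only 5 years. The competing horizon comes from 8.1 and the interim text.
- Section 8.1 does not say that the extension depends on results. A reader might infer that the committee would choose the horizon because its members know the allocation. Knowing individual allocations is not knowing aggregate outcomes, so 8.1 alone does not support this. The concern about a data-dependent choice rests on the interim text.
- A reader might infer that a 3-year stop loses the later deaths. Section 11 says dates of death reach the registry automatically from the Swedish death registry, so for Swedish patients they remain retrievable.
- A reader might compute a firm loss of OS power by taking 46% as control 3-year OS and the hazard ratio of 0.81 in Section 16.3: 164 against 224 deaths, power 27% against 35%. The 46% comes from 37 patients in the mixed cohort. The 0.81 is tied to Figure 1, which Section 5.2 introduces for RFS, and it is not identified as an OS hazard ratio. Neither is a design input.
- Substantial changes made at the interim go to the authorities as an amendment. That documents the choice but does not make it independent of the data.

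**Conclusion.** The contradiction is real and stands in current text. Two sentences leave the OS/RFS horizon at 3 years or undecided, while the rest of the protocol fixes 5. As written, the horizon can be settled after OS and RFS have been reviewed in an open-label trial, by a body the protocol does not name consistently.

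The size is illustrative only. Under exponential survival with an assumed 3-year OS of 46-50%, roughly a quarter of 5-year deaths fall in years 3-5. The range is about 18-33% with a per-patient horizon, slightly wider at the top if the hazard rises with time, and about 15-17% with a common cut-off. The issue is which deaths count in the pre-specified analysis, not irrecoverable data.

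The current primary endpoint and the 326 patients are unaffected. That would change only if OS became primary. The struck-out RFS analysis text in 13.2.1 refers to an appendix that is not in the document at hand. It may settle the RFS horizon for analysis, but 8.1 and the interim text would still need to agree with it.

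**What to change.** - Section 8.1: state that OS and RFS are followed for 5 years in every patient and quality of life for 3 years. Delete the study committee's option.
- Section 13.2.1, Interim analysis: delete the sentence that defers the choice between 3 and 5 years.
- Label any 3-year report of OS or RFS as a preliminary cut of the 5-year analysis.

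The cost is two edits in the next amendment. No visit is added, because year 5 is already in Table 3 and fits the 2021-2029 study period. There are two downsides. The final secondary report cannot be brought forward to year 3. Five-year vital status must also be obtained for any non-Swedish site: Aarhus and Oslo are listed as pending, and no automatic death link is described for them.
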